### Data collection

2.8

All the information will be collected from each participant that consists of patient's background, medical history, medication, blood samples, ECG, echocardiography. The study group will be follow-up for MACCE evaluation after pPCI.

### Sample size

2.9

The protocol planned to enroll 300 participants including 200 NSTEMI patients in the Study group and 100 healthy individuals in the Control group. The ratio of 2:1 sample size will provide 80% power to detect an absolute difference of TMAO and TML biomarkers between the 2 groups. The 200 NSTEMI patients with given a 10% rate of loss during follow-up for MACCEs as secondary endpoints will provide 80% power at a two-sided significance level of 0.05.

### Statistical analysis

2.10

Continuous variables will be expressed as mean ± standard deviation or median with interquartile range, whereas categorical data will be expressed as percentages. Continuous variables will be analyzed using *t* tests or Fisher exact or Pearson χ^2^ tests for categorical variables as appropriate. Kolmogorov-Smirnov test will be performed for normality. Pearson and Spearman correlation analyses will be used to examine the correlations between TMAO and TML levels, SYNTAX score and the numbers of diseased coronary vessels. Ordinal logistic regression analyses with adjustments for traditional risk factors (including age, sex, hypertension, diabetes mellitus, smoking, low-density lipoprotein cholesterol level, high-density lipoprotein cholesterol level, and triglyceride and body mass index) will be used to determine the association of TMAO and TML with a high SYNTAX score and the presence of multiple vessel diseases. Kaplan-Meier curves will be used for correlation of TMAO and TML with the short and long-term MACCE rate after the pPCI. A *P* value ≤ .05 will be considered statistically significant. All statistical analyses will be performed with SPSS 25 (IBM).

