### Study objective

1.2

The primary objective of the study is to evaluate the relationship between TMAO and TML levels with the extent of an atherosclerotic burden as quantified by the number of diseased coronary vessels and the SYNTAX score in NSTEMI patients.

The secondary objective of the study is to assess TMAO and TML as prognostic biomarkers for the short (1 month) and long-term (12 months) MACCE rate after the pPCI in NSTEMI patients.

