### Study procedures

2.4

The following information will be obtained from all individuals including baseline demographic, present and past medical history, physical examination findings, 12 lead ECG, and cardiovascular risk factors before enrollment.

Diagnostic CAG and pPCI procedures will be performed by the redial approach within 24 hours of admission under the Fuwai Hospital standard protocol. Multiple diagnostic CAG views will be obtained, for the left anterior descending and left circumflex coronary at least four projections, and the right coronary artery at least two projections. All patients will be received standard oral dual antiplatelet therapy with 300 mg of aspirin (follow by 75–100 mg daily) and 600 mg of clopidogrel (follow by 75 mg daily for ≥ 12 months) as well as intravascular infusions of 70 to 100 IU/kg of unfractionated to weight and boost the operation progressed. During pPCI, the choice and selection of balloons, guide wires, type and size of stents will be determined by the operator.

For primary endpoints, 2 experienced interventional cardiologists blinded to study protocol will evaluate the atherosclerotic burden by the SYNTAX score after the CAG. The SYNTAX score will be calculated from the official SYNTAX score website (www.syntaxscore.com/calculator/syntaxscore/frameset.htm) for each NSTEMI patient. All patients will be divided into two groups according to SYNTAX score including low–intermediate risk (SYNTAX score < 22) and high-risk (SYNTAX score ≥22). The opinion of a third interventional cardiologist will be taken if there is any discrepancy between the results of the SYNTAX score. Moreover, a single vessel disease or multiple vessel diseases will be defined as one or more major coronary vessels exhibiting ≥70% stenosis after the procedure.

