### Study outcomes

2.6

The primary endpoint of the study will be assessed an association of TMAO and TML with coronary atherosclerotic severity quantify by the number of diseased coronary arteries, SYNTAX scores after the CAG. For secondary endpoints in Study group, the plasma TMAO and TML will be used as prognostic biomarkers for MACCEs including myocardial infarction, target vessel revascularization, stroke, heart failure, all-cause re-hospitalization and all-cause mortality at the short (1 month) and long-term (12 months) after the pPCI. Each patient in the Study group will be scheduled for follow-up at 1, 3, 6, and 12 months after pPCI at Fuwai hospital by a trained team of cardiologists to identify MACCEs and further clinical consultation.

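### The only covariate-adjusted analysis of the primary endpoint is an ordinal model fitted to two two-level outcomes, so no adjusted estimate exists on the SYNTAX score or vessel count themselves

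*Protocol article*

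**What the plan says.** All references are to the protocol article.

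- **Endpoint.** Section 1.2 sets the primary objective on atherosclerotic burden "as quantified by the number of diseased coronary vessels and the SYNTAX score in NSTEMI patients". Section 2.6 repeats this for the primary endpoint: severity is to be "quantify by the number of diseased coronary arteries, SYNTAX scores after the CAG". Both describe a score and a count.
- **Categories.** Section 2.4 states "All patients will be divided into two groups according to SYNTAX score", with the boundary at 22. It also says that "a single vessel disease or multiple vessel diseases will be defined as one or more major coronary vessels exhibiting ≥70% stenosis", which I read as one diseased vessel versus more than one.
- **Adjusted analysis.** Section 2.10 names "Ordinal logistic regression analyses with adjustments for traditional risk factors", lists nine covariates, and says that these analyses "will be used to determine the association of TMAO and TML with a high SYNTAX score and the presence of multiple vessel diseases".
- **Full-scale analysis.** The preceding sentence of section 2.10 plans Pearson and Spearman analyses "to examine the correlations between TMAO and TML levels, SYNTAX score and the numbers of diseased coronary vessels". No adjustment is attached to these.

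**The concern.** The endpoint is a score and a count, but the model that adjusts for age, sex, diabetes, lipids and the other listed factors sees only which side of a boundary each patient falls on. A patient just above 22 and one far above it count the same, as do patients with two and three diseased vessels.

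The method name points to ordered categories and the outcomes do not. A reader cannot tell whether ordered categories were meant and lost in the text, or binary models were meant and misnamed.

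What is at stake is precision and match. The adjusted result separates the biomarkers from known risk factors, and it is the one computed on reduced data. The sample-size section states power for the patient-control difference and for MACCEs only, so nothing shows that the association with burden can absorb the loss.

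**Working it through.** **The plan's own figure.** Section 2.9 states 80% power but gives no difference or standard deviation, and the statement does not concern this model. With 200 versus 100 and two-sided 0.05, 80% power corresponds to a standardised difference of (1.960 + 0.842) × √(1/100 + 1/200) = 0.343. That says nothing about the adjusted SYNTAX or vessel analysis, so there is no stated figure to reproduce here.

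**Step 1: ordinal regression with two levels.** The proportional-odds model has one threshold per boundary between categories. Two categories leave one threshold, which is the binary logistic intercept with its sign reversed. Fitting both models to the same simulated two-level outcome (200 patients, two predictors) gave slopes 0.900 and 0.249 with standard errors 0.211 and 0.195 from each. The label is therefore a mismatch in specification and changes no number.

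**Step 2: information kept when SYNTAX is cut at 22.** The share p with a score ≥22 is not in the article, so p is an assumption. Two standard approximations were used:

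- normal score: φ(z)² / [p(1−p)], where z cuts off the upper share p
- proportional odds against an effectively continuous score: 3p(1−p)

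Example at p = 0.20: z = 0.842 and φ(z) = 0.280, so 0.0784 / 0.16 = 0.49. The second formula gives 3 × 0.2 × 0.8 = 0.48.

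| Assumed share ≥22 | Loss, normal | Loss, proportional odds | Power if full score had 80% (normal) |
|---|---|---|---|
| 10% | 66% | 73% | 37% |
| 20% | 51% | 52% | 50% |
| 25% | 46% | 44% | 54% |
| 30% | 42% | 37% | 57% |
| 50% | 36% | 25% | 61% |

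The last column is Φ(2.802 × √kept − 1.960).

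**Step 3: information lost when a 1/2/3 vessel count becomes single/multiple.** The share kept is [1 − p₁³ − (1−p₁)³] / [1 − Σpₖ³]. The distribution is again an assumption. Example at 40/35/25%: (1 − 0.064 − 0.216) / (1 − 0.064 − 0.0429 − 0.0156) = 0.72 / 0.8775 = 0.82, a loss of 18%.

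| Assumed 1/2/3 vessels | Loss |
|---|---|
| 60/25/15% | 6% |
| 50/30/20% | 11% |
| 40/35/25% | 18% |
| equal thirds | 25% |
| 30/35/35% | 29% |
| 20/30/50% | 43% |
| 20/40/40% | 44% |

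**Step 4: events per model term.** Nine listed covariates plus one biomarker make 10 terms. With 200 patients, 20%, 30% and 50% high SYNTAX give 40, 60 and 100 events, or 4, 6 and 10 per term.

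**The case against.** The strongest reply is that the plan does analyse both full scales. The correlations use the score and the count directly, and the objective asks only for a relationship. That stands as far as it goes: a reader might infer that the plan throws the score and count away, and the text does not support this. Only the adjusted model drops them. The reply does not reach adjustment, because nothing in section 2.10 extends the covariates to the full scales.

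The cuts are also fixed in advance and have a purpose. The discussion wants to separate low-risk from high-risk patients, and it cites a 335-patient STEMI cohort that reported SYNTAX burden and multi-vessel disease. This is a good reason to keep the split analyses, but not to make them the only adjusted ones.

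Three stronger readings are tempting and unsupported:

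- **That about half the information is lost.** This fits SYNTAX only if roughly 20-25% of patients score ≥22, and it overstates most vessel splits.
- **That the model must be overfitted, because excluding left main lesions keeps high scores rare.** The article gives no figure for how many patients reach 22. Four events per term is one assumed case, and ten is another.
- **That the trial's claim of an independent association rests on this model.** The article uses that word for earlier studies. For its own aims it speaks of association and prediction, and it does not name the adjusted model as the primary analysis.

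**Conclusion.** The point holds in a limited form. The endpoint is a score and a count. The one adjusted model named for it uses two-level versions of both under a method name that does not fit them, and the full scales receive only unadjusted correlation.

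The size depends on shares that the article does not give. The SYNTAX cut costs about 25-73% of the information for 10-50% of patients scoring ≥22 (36-51% for 20-50% under a normal score). The vessel split costs about 6-44% across the assumed distributions. These figures are approximations for modest associations, and the normal formula will be off if the score is skewed. Within these ranges the SYNTAX loss is never below a quarter, whereas the vessel loss can be small.

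This is a change that should be made for precision and for consistency with the endpoint. It is not a numerical error in the plan.

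**What to change.** In section 2.10, state the adjusted analyses of the primary endpoint as:

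1. the SYNTAX score on its full scale, by proportional-odds regression or a linear model on a suitable scale; and
2. proportional-odds regression on the ordered number of diseased vessels (1, 2, 3).

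Both carry the covariates already listed. Keep SYNTAX ≥22 versus <22 and multiple versus single vessel disease as supportive analyses, and call them binary logistic regression. The named ordinal method then has an ordinal outcome.

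The cost is wording only. The score is calculated for every patient and the vessel count is already needed for the planned correlations, so no new data or patients are required. The drawback is that the main estimate is less directly an odds ratio for high SYNTAX. That odds ratio remains available from the supportive model, which also preserves comparison with the cited STEMI cohort.

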### Blood sampling and biomarkers measurement

2.5

Routine and biochemical blood tests will be measured from venous blood samples obtained in a fasting state on the morning following the admission day or before the procedure. An extra EDTA blood sample will also be obtained from each included individual and centrifuged immediately at 2500 g for 10 minutes at room temperature and stored at –80^o^C incubator for later analysis. The plasma TMAO and TML will be measured by isotope dilution high-performance liquid chromatography with online tandem mass spectrometry on an API 3200 triple quadra pole mass spectrometer (AB SCIEX, Framingham, MA) as previously described.^[13–15]^ Laboratory personnel who analyze TMAO, TML and other routine laboratory tests will be blinded to individual characteristics.

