## Conclusions

4

The SZ-NSTEMI will be the first cohort that will investigate the association of TMAO and TML with the severity and prognosis of coronary atherosclerotic burden in NSTEMI patients, aiming to identify TMAO and TML as predictors and prognostic biomarkers.

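### The prognostic aim is given only unadjusted Kaplan-Meier curves, which group continuous markers and can show only a crude association with MACCE, while the severity analysis is adjusted for nine risk factors

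*Protocol article*

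**What the plan says.** The Study objective section (1.2) sets the secondary aim: to "assess TMAO and TML as prognostic biomarkers for the short (1 month) and long-term (12 months) MACCE rate after the pPCI". The Conclusions repeat the ambition, "aiming to identify TMAO and TML as predictors and prognostic biomarkers".

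The Statistical analysis section (2.10) assigns methods by endpoint.

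- **Severity of disease:** "Ordinal logistic regression analyses with adjustments for traditional risk factors" will examine the "association of TMAO and TML with a high SYNTAX score and the presence of multiple vessel diseases". Nine factors are listed: age, sex, hypertension, diabetes, smoking, LDL cholesterol, HDL cholesterol, triglyceride and body mass index.
- **MACCE:** "Kaplan-Meier curves will be used for correlation of TMAO and TML with the short and long-term MACCE rate after the pPCI". The article names no covariate, regression model or marker grouping for this endpoint.

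**The concern.** Kaplan-Meier curves estimate event-free proportions within groups. They do not measure correlation with a continuous marker, so TMAO and TML must first be cut, and the result is a comparison with no adjustment.

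That matters here because the primary hypothesis is that TMAO and TML rise with SYNTAX score and number of diseased vessels. If they do, patients with high and low marker values may also differ in age, diabetes and other drivers of events. Separated curves could then arise with no prognostic information in the marker itself. The Discussion expects the results to help sort patients by risk and perhaps influence treatment. A crude split supports that use poorly. Grouping also discards information from however many events there are.

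**Working it through.** **The plan's own figure.** The Sample size section (2.9) makes this statement about the study group: "with given a 10% rate of loss during follow-up for MACCEs as secondary endpoints will provide 80% power at a two-sided significance level of 0.05". This 80% can be neither reproduced nor refuted, because the article gives no event rate, hazard ratio or marker grouping. The check therefore asks which hazard ratio (HR) is detectable under assumed event rates.

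**Inputs from the article.** 200 patients with 10% loss give 200 × 0.9 = 180 evaluable. Power is 80% and alpha is two-sided 0.05, so the normal quantiles sum to 1.960 + 0.842 = 2.802. The markers are measured on a continuous scale: "The plasma TMAO and TML will be measured by isotope dilution high-performance liquid chromatography".

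**Assumptions not in the article.** 12-month MACCE in 10% to 40% of patients (D = 18 to 72 events); a marker that is normal after log transformation, with a log-linear effect; a median split for the curves, compared by a log-rank test.

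**Formulas.**

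- Median split, HR between halves: exp(2 × 2.802 / √D).
- The same per SD: the halves of a standard normal marker differ in mean by 2√(2/π) = 1.596 SD, so divide the log HR by 1.596. This equals keeping 2/π = 0.637 of the information; 180 patients act like about 115.
- Continuous term, unadjusted, HR per SD: exp(2.802 / √D).
- Continuous term, adjusted: replace D by D(1 − R²), where R² is the share of marker variance explained by the covariates.

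For D = 36:

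- Split: exp(2 × 2.802 / 6) = exp(0.934) = 2.54 between halves. Per SD, exp(0.934 / 1.596) = 1.80.
- Continuous: exp(2.802 / 6) = 1.60.
- Adjusted, R² = 0.2: 36 × 0.8 = 28.8 effective events, and exp(2.802 / √28.8) = 1.69.

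| Events (rate) | Split, HR between halves | Split, per SD | Continuous, per SD | Continuous, R² = 0.2, per SD |
|---|---|---|---|---|
| 18 (10%) | 3.75 | 2.29 | 1.94 | 2.09 |
| 36 (20%) | 2.54 | 1.80 | 1.60 | 1.69 |
| 54 (30%) | 2.14 | 1.61 | 1.46 | 1.53 |
| 72 (40%) | 1.94 | 1.51 | 1.39 | 1.45 |

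The precision gain vanishes when 1 − R² = 2/π, that is, at R² of about 0.36.

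**Effect of not adjusting.** A simulation used 180 patients, about 20% events and 1000 runs per setting. The marker had no effect of its own but was correlated 0.2 to 0.4 with one prognostic covariate (HR 1.5 to 2.0 per SD). The unadjusted log-rank test at the median was significant in 7% to 25% of runs. The Cox model adjusted for that covariate was significant in 5% to 6%. The crude test is not invalid here, because a crude association does exist. The result shows how often crude curves would be read as evidence about the marker when the covariate is responsible.

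**The case against.** The strongest reply is that this is a condensed article and a fuller analysis plan may exist. The article does not say that Kaplan-Meier is the only MACCE analysis, and a cut-point is a detail commonly left to such a plan. A reader might infer that the cut will be picked after seeing the outcomes; nothing in the article supports that. What stands is narrower. The article specifies adjustment, with covariates, for severity and a different, unadjusted method for MACCE, so the mismatch is in stated text.

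A reader might also infer that the study claims independent or incremental prognostic value for MACCE and cannot deliver it. The objective and Conclusions say only prognostic, and grouped curves can show a crude form of that. The Background does cite earlier work on these markers as independent predictors, and the Discussion cites associations that survived adjustment, so adjustment is a natural standard for the study, but the aim does not state it.

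Three further points limit the size of the problem.

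- The exclusions (severe renal disease, heart failure, atrial fibrillation, left main lesions) and the upper age limit of 75 narrow confounding without removing it.
- SYNTAX score may lie on the causal pathway, since the Discussion says TMAO promotes atherosclerosis. Failing to separate the marker from it is not simply confounding.
- The efficiency loss depends on a median split that the article does not specify. Scored tertiles keep about 79%: at 36 events, exp(2.802 / √(36 × 0.79)) = 1.69 per SD. MACCE also includes all-cause rehospitalization, so events may be more numerous than assumed.

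**Conclusion.** The concern holds in a limited form. As written, the prognostic aim would yield only a crude, grouped comparison, while the severity aim in the same section is adjusted for nine factors. A difference in MACCE between marker groups could not be told apart from differences in age, diabetes or other shared risk factors.

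The main loss is interpretability. The gain in precision is moderate and conditional: at an assumed 36 events, about 1.80 per SD for a median split against 1.60 for a continuous term, or 1.69 with adjustment at an assumed R² of 0.2. Event rates, split and R² are all assumptions.

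This should be fixed. It is not critical, because it concerns a secondary aim of an observational cohort, does not affect the primary endpoint, and might be met by an analysis plan not shown.

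**What to change.** Before outcomes are examined, state the following.

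- **Main 12-month analysis:** a Cox model for MACCE with log-transformed TMAO as a continuous term, and TML in a separate model. Report the HR with its 95% CI.
- **Covariates:** a short, pre-fixed set sized to the events, for example age, diabetes, and renal function if creatinine is in the biochemistry panel (the article names neither creatinine nor eGFR). The full nine-factor list would be too long: with 36 events, nine covariates plus the marker leave 36 / 10 = 3.6 events per term, against 36 / 4 = 9 with three covariates.
- **Second model:** add SYNTAX score, interpreted with care because it may be a mediator.
- **Display:** Kaplan-Meier curves at a split fixed in advance.
- **1 month:** keep the stated objective.

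The cost is a few more lines of analysis and some precision lost to adjustment. Age and diabetes are already in the planned covariate list, so the core model needs no new data.

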## Discussion

3

The use of novel biomarkers has transformed cardiovascular medicine both in diagnosis and risk assessments.^[14,17–20]^ Current risk stratification markers of myocardial necrosis indicate predominantly the short-term adverse risks and recognize those individuals for whom more invasive diagnostic testing and revascularization may be reasonable.^[17–20]^ The traditional CVD risk biomarkers including cholesterol, triglycerides, high-sensitivity C- reactive protein have the ability for long-term risk prediction.^[20]^ There is limited data that could be utilized biomarkers for the prediction of high-risk CVD patients and their prognostic evaluation of the short and long-term outcomes.^[17–20]^ Identification of novel biomarkers that may predict myocardial necrosis as well as provide both short and long-term prognostic values in CVD particularly NSTEMI subjects is alike of interest, as this may enable us to recognize pathways related to CVD pathogenesis, as well as enhanced potential preventive CV risk reduction efforts.^[17–20]^ Here, this proposed SZ-NSTEMI protocol is ongoing which aims to investigate the relationship of TMAO and TML with atherosclerosis burden and prognostic risk ability in NSTEMI patients.

TMAO is the gut microbiota derived from dietary trimethylamines-containing nutrients (mainly choline, phosphatidylcholine, L-carnitine).^[7]^ TMAO promotes macrophages foam cell formation, development of platelet hyperactivity, altered bile acids, and cholesterol transport, and activation of the inflammatory pathway.^[7–13]^ All these factors are linked with an increased risk of many types of cardiovascular diseases including atherosclerosis, stroke, congestive heart failure, atrial fibrillation, and chronic kidney disease.^[7–13]^ TML is a precursor of TMAO was also found alone and together with TMAO with increased risk of short and long-term CVD events in patients with chest pain and STEMI.^[14]^ In animal studies found that TMAO promotes atherosclerosis by inhibiting reverse cholesterol transport, activating macrophages, and increasing platelet activity and thrombosis, whereas inhibiting TMAO production decreases the formation of atherosclerotic lesions.^[8–12]^ Many clinical studies also confirmed the association of TMAO and its precursor TML metabolites with CVD risks after adjusting the traditional risk factors.^[7,13–15]^

More recently, it has been further confirmed that long-term increases in TMAO were related to a greater risk of CVD and repeated assessment of TMAO over 10 years improved the identification of individuals with a higher risk of CVD.^[21]^ A Chinese cohort of 335 STEMI patients found that higher TMAO levels are significantly associated with high atherosclerotic burden assessed by SYNTAX score and multi-vessel disease.^[15]^ Another prospective series of 211 patients with STEMI demonstrated higher TMAO levels association with plaque rupture assessed by optical coherence tomography examination and these findings have significant adverse risks in CVD patients.^[22]^ The association of TMAO with atherosclerosis burden in stable coronary artery disease has also been reported previously.^[21]^ In light of these promising findings, the evaluation TMAO and TML are warranted in NSTEMI patients as represent the most frequent group of CVD patients undergoing pPCI, which may serve as a potential target for atherosclerosis prevention and treatment as compared with present traditional treatments. Here, the SZ-NSTEMI cohort is underway to evaluate TMAO and TML in NSTEMI patients, which may further enable us to stratify low and high-risk patients and may impact the short and long-term treatment protocol at the clinical setting.

As for the limitations, the study will carry out at a single center with a comparable number of NSTEMI patients. Moreover, TMAO and TML are gut microbes that may have the potential to be influenced by nutritional status and diet. However, this study protocol will be unable to evaluate the nutritional status of each participant before enrollment and that may bias the results.

